### Outcome measures

Therapeutic evaluation will be carried out by the same team member who will be blinded to treatment allocation. The primary evaluation index of this study will be change of gait in PD patients, whereas the secondary evaluation indices will include evaluation of limb function, activity of daily life, and fall risk. We will adopt a three-dimensional gait analysis system for evaluation of gait information and surface electromyography for muscles related to lower limbs. We will employ the Unified Parkinson’s Disease Rating Scale (UPDRS) to assess the mental cognition, motor function, and daily living ability [22], while the Fall Efficacy Scale (FES) will be used to assess the risk of falls. Data across all measurements will be recorded in the data center [23].

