### Sample size

This will be a randomized controlled trial, seeking to evaluate efficacy of three methods for treatment of Parkinson’s FOG. The main observation index will be gait parameters. Since there is no three-dimensional gait analysis result to evaluate the effect of music exercise therapy on Parkinson’s FOG, before this study, we will temporarily use results of the unified Parkinson’s disease assessment scale (UPDRS III) from our preliminary trial for calculations. According to the pretrial, the mean value of UPDRS (III) score reduction of three groups, after treatment, is predicted to be 20.7 ± 16.6, 7.9 ± 6.3 and 2.6 ± 2.2, respectively. We will perform a two-sided test, with *α* and assurance (test efficiency) of 0.05 and 90%, respectively. According to calculations from the Pass software method (Pass15), our sample size will be 66 cases. However, we will enroll at least 81 cases, due to a 20% drop out rate.

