### Analysis of primary and secondary outcome measures

Analysis of categorical variables will be performed using the Pearson’s *χ*^2^ or Fisher’s exact tests, whereas continuous variables will be analyzed using a Student’s *t* test or appropriate non-parametric methods. All datasets will be analyzed at 95% confidence interval and will be tested by double-sided statistics. Data will be expressed as means ± standard deviation (SD). Data will first be tested for normality and homogeneity of variance prior to analysis, and if the normal distribution is satisfied, a *t* test will be used to compare 2 groups, whereas analysis of variance (ANOVA) with LSD or SNK methods will be used for multiple comparisons. Datasets that are not normally distributed will be analyzed using a rank sum test.

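### Homogeneity of variance is tested but the result changes nothing: normal data with unequal spread still go to pooled-error ANOVA with LSD or SNK

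*Protocol article*

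**What the plan says.** The section Analysis of primary and secondary outcome measures has both normality and homogeneity of variance checked before analysis. What follows depends on normality alone. If it is satisfied, two groups are compared by a t test, and "analysis of variance (ANOVA) with LSD or SNK methods will be used for multiple comparisons". The one alternative is for non-normality: "Datasets that are not normally distributed will be analyzed using a rank sum test". Nothing is said about what happens if the variances are found unequal.

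The Sample size section gives the only planning figures. The mean UPDRS III reduction in the three groups "is predicted to be 20.7 ± 16.6, 7.9 ± 6.3 and 2.6 ± 2.2, respectively". These stand in for gait data that did not exist: "we will temporarily use results of the unified Parkinson’s disease assessment scale (UPDRS III) from our preliminary trial for calculations". The Outcome measures section states that "The primary evaluation index of this study will be change of gait in PD patients" and uses UPDRS for secondary assessments.

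**The concern.** LSD and SNK take one error variance, pooled over all three arms, and apply it to every pair. That is sound if the arms have similar spread. On the plan's own figures they do not. The music arm has by far the largest variance, so the pooled error is too small for comparisons that involve music and far too large for exercise versus control.

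Two conclusions are at stake. Music versus exercise is the contrast that isolates the music component, and it would be tested too liberally. Exercise versus control would lose most of its power, so a real exercise effect would usually be reported as no difference. Both errors favour music.

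The same section also allows a two-group t test, which uses only the two arms compared. One contrast can therefore be tested with two very different standard errors, and the text does not say which applies.

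**Working it through.** **Inputs (Sample size section).** Means 20.7, 7.9, 2.6 and SDs 16.6, 6.3, 2.2, taken in the order music exercise, exercise, control. Two-sided alpha 0.05 and 90% power. 66 evaluable patients, so 22 per arm at 1:1:1. 81 enrolled, so 27 per arm if nobody drops out.

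**The plan's own figure.** "our sample size will be 66 cases" reproduces. A one-way ANOVA with these means and a common SD of 16.6 needs 22 per arm (power 0.912). A two-sample t test of music versus exercise with their own SDs also needs 22 per arm.

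**Standard errors at 22 per arm.**
- Variances: 275.56, 39.69, 4.84. Ratio of largest to smallest: 275.56/4.84 = 57.
- Pooled SD: √((275.56 + 39.69 + 4.84)/3) = 10.33.
- Pooled SE, used for every pair: 10.33 × √(2/22) = 3.11.
- True SE, music versus exercise: √((275.56 + 39.69)/22) = 3.79. The pooled SE is 0.82 of this.
- True SE, exercise versus control: √((39.69 + 4.84)/22) = 1.42. The pooled SE is 2.19 times this.

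**Check by hand.** With 63 error degrees of freedom the t critical value is 2.00, so LSD needs a difference of about 2.00 × 3.11 = 6.2 points. The planned exercise versus control difference is 7.9 − 2.6 = 5.3, below that threshold, so power must be under 50%. For music versus exercise, the normal approximation to the type I error is 2 × (1 − Φ(1.96 × 0.82)), about 11%.

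**Simulation** (400,000 normal data sets per scenario, the three SDs above, 22 per arm unless stated):

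| Quantity | LSD, no F test first | LSD after significant F | SNK | Welch t |
|---|---|---|---|---|
| Power, exercise vs control, planned means | 30.0% | 30.0% | 30.0% | 94.8% |
| Same, 27 per arm | 43.0% | 43.0% | 43.0% | 98.0% |
| Power, music vs exercise, planned means | 95.7% | 95.7% | 95.7% | 90.3% |
| Type I error, music vs exercise, all means equal | 11.2% | 7.5% | 6.6% | 5.1% |
| Same, both at 7.9, control 2.6 | 11.2% | 9.6% | 9.2% | 5.0% |
| Same, both at 20.7, control 2.6 | 11.2% | 11.2% | 11.2% | 5.0% |

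**Would the variance check notice?** Yes. Levene and Brown-Forsythe tests rejected homogeneity in all 20,000 simulated data sets at both sample sizes.

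**The permitted two-group t test.** An ordinary Student t test on the two arms alone gives about 5.4% type I error for music versus exercise and 95.2% power for exercise versus control, nearly the same as Welch.

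**Games-Howell.** This adjusts for three comparisons and so costs more than unadjusted Welch tests. A separate simulation (100,000 data sets, same inputs) gives 81% power for music versus exercise and 88% for exercise versus control at 22 per arm, and 90% and 95% at 27. Welch t tests allowed only after a significant Welch ANOVA keep 90% and 95% at 22.

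**The case against.** The strongest reply is that the plan does check homogeneity, that with these SDs the check would practically always fail, and that what to do next is a detail for the statistical analysis plan, which is not shown. It is true that the plan does not overlook unequal variances, and the analysis plan may settle the matter. But the article does not leave the method open. It names the tests and the branching rule, and an analysis plan that followed that rule would carry the fault over.

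Other points stand and limit the finding:

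- **Endpoint.** The SDs are for UPDRS III. A reader might take 11% and 30% as properties of the primary analysis. The documents do not support that, because no SD is given for any gait parameter.
- **Skewed data.** Each SD is about 0.8 times its mean, so skew is plausible, and a reader might infer that LSD fails there too. Non-normal data leave the LSD route. With gamma data of the same means and SDs, Shapiro-Wilk rejected normality in at least one arm in 98% of 4,000 simulated trials, and the rank sum test had 98% power for exercise versus control.
- **How normality is checked.** If it is checked on pooled residuals, unequal spread alone fails the check in 97% of trials. The rank sum test then has 93% power for exercise versus control and rejects 6.6% for music versus exercise with equal means. Checked arm by arm, only 15% of trials fail. The article does not say which is meant.
- **Two-group t test.** If this is the intended pairwise route, the fault largely disappears. The text does not say that it is.

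**Conclusion.** The point holds as a defect in a stated rule: the homogeneity test has no consequence, and normal data with unequal variances go to a pooled-error method.

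Its size is known only for UPDRS III. The power loss for exercise versus control (30% at 22 per arm, 43% if all 81 complete, against 95% and 98% with Welch) is the firmer figure, because it uses the planned means and SDs as they stand. It assumes normal data that reach LSD or SNK.

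The type I error of about 7–11% for music versus exercise is less certain. It assumes that the SDs stay unequal when the means are equal, although the planned SDs rise with the means. It also depends on whether an F test comes first and on the control mean. A flat claim that the false-positive rate doubles is therefore more than the documents support: 11% is the upper end.

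For the primary gait outcome the missing branch applies equally, but its effect cannot be quantified.

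**What to change.** In Analysis of primary and secondary outcome measures, replace ANOVA with LSD or SNK by a method that does not assume equal variances for every continuous outcome on the parametric route, and name one route for the pairwise contrasts. For example: the three groups are compared by Welch ANOVA and, if it is significant at the two-sided 5% level, each pair by a Welch t test. Welch ANOVA with Games-Howell is the alternative. The result of the homogeneity test then no longer matters, and the choice between the t test and the three-group method is closed.

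The cost is one sentence here and in the statistical analysis plan, agreed before allocations are released. It needs no extra patients or data. With the Welch t tests, nominal power for music versus exercise at 22 per arm is about 90%, the planned level, instead of 96% from a standard error that is too small. With Games-Howell it is about 81% at 22 per arm and 90% at 27, so that option should be chosen knowingly.

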### Interim analyses

No interim analyses are planned.

### Methods for additional analyses (e.g., subgroup analyses)

Not applicable.

### Methods to handle protocol non-adherence and missing data

Analyses will be performed according to the intention-to-treat principle.

### Plans to give access to the full protocol, participant-level data, and statistical code

The full protocol, participant-level data, and statistical code will be available from the corresponding author, upon reasonable request.

## Oversight and monitoring

### Composition of the coordinating center and trial steering committee

The Trial Steering Committee (TSC) will comprise chief principals, investigators, a statistician, and trial manager.

### Composition of the data monitoring committee, its role and reporting structure

The TSC will be in charge of data monitoring.

### Adverse event (AE) reporting and harms

Any adverse medical events to the participants will be collected after the subjects have signed the informed consent and agreed to participate in the study. Events will not be considered to be related to music exercise therapy if they occur after the participant has signed the informed consent, but before the intervention. All adverse events occurring after enrolment into the study and before discharge will be recorded and reported to the local Institutional Review Board.

### Frequency and plans for auditing trial conduct

We will conduct systematic and independent supervision on trial-related activities and documents, to determine whether implementation of the trial as well as data recording, analysis, and reporting are in line with the trial protocol, the sponsor’s standard operating procedures (SOP), good clinical practice (GCP), and applicable management requirements. The TSC will have biweekly meetings, to discuss and monitor progress of the trial.

### Ethics and dissemination

Any significant modifications to the trial protocol will require ethical review.

### Dissemination policy

Study findings will be widely disseminated through manuscript publication in a high-impact peer-reviewed journal.

### Plans for communicating important protocol amendments to relevant parties (e.g., trial participants and ethical committees)

All substantial protocol amendments will be made by the principal investigators, following approval from IRB and the ethics committee.

## Discussion

FOG, the most common gait abnormality that occurs during mid and late stages of Parkinson’s disease, can lead to falls and injuries. To date, drug treatment has not effectively managed the disease although rehabilitation treatment has shown significant promise. Early recognition and intervention of FOG can reduce disability rate and improve prognosis. Results from our pilot study showed that music exercise therapy can improve the FOG of Parkinson’s patients and improve their quality of life. However, its long-term effects are not known, necessitating further research. Therefore, we propose a prospective randomized clinical trial to validate the clinical efficacy of music exercise therapy for treatment of FOG in Parkinson’s patients.

To eliminate the interference of headphone wearing behavior on test results, we have proposed a set of exercises without music. Bias exists in all clinical trials. Therefore, we acknowledge that blinding music therapists and patients to the intervention will be the most challenging aspect during designing of this randomized controlled trial. Consequently, we will blind our evaluators to minimize potential bias and further adopt a three-dimensional gait analysis as part of the approach for evaluating our results. Previous studies have widely used this analysis system to evaluate gait, especially in neurological diseases. We will also apply time and space and ankle kinematic parameters as well as electrophysiological measurements during the process of walking, and this is expected to provide quantitative information about gait and reduce the interference of subjective factors in the scale evaluation. We believe that our findings will help improve FOG and motor function in patients with Parkinson’s disease.

## Trial status

The total registration period will last for 2 years, while the follow-up will be for 3 months. Patient recruitment began on January 1, 2020, and the trial is currently underway. Protocol version number and date: V1.0, May 16, 2020. Recruitment of patients is expected to be completed in December 2021.

## Data Availability

Data sharing is not applicable to this article as no datasets have so far been generated or analyzed.
